### Unblinding {17b}

The design is open label with only data analysts being blinded so unblinding will not occur.

## Data collection, management, and analysis

### Data collection methods {18a}

The questionnaire data will be entered by the research team at the University Hospital of Cologne who are not involved in consultation and recruitment of patients.

### Participant retention and complete follow-up {18b}

Study participants in both intervention and control groups will receive postal reminders when questionnaires have not been sent back in 1 week and over the phone reminders when questionnaires have not been sent back in 2 weeks to promote participant retention and minimize dropouts.

### Data management {19}

The software Remark office will be used to extract pseudonymized data from the questionnaire with two independent members of the research team manually verifying the extracted data. The paper-based questionnaires will be kept in locked storage in accordance with German law. The extracted data will be stored in password-protected files on password-protected computers only accessible by the research team.

### Confidentiality {27}

Personal information and the data obtained by the participants will be kept and stored separately. Only the recruiting physicians will have a list that allows matching of study ID and personal information. This list will be kept strictly confidential and only be accessible by recruiting physicians in their respective study center. The research team will only receive pseudonymized questionnaire data.

### Biological specimens {33}

No biological specimens will be collected.

## Statistical methods

### Statistical methods {20a}

Baseline data will be analyzed to guarantee comparability of both groups. Mean differences of the primary outcome in both groups (congruence between preferred role at baseline and actual role in the decision-making process at t1) will be compared using an independent samples one-sided *t*-test with the group allocation as the independent variable. All secondary outcomes will be analyzed via independent samples *t*-tests, Chi-square tests, or nonparametric tests in case of non-normality. Beyond group allocation, demographic data will be used as the independent variable. All data analysis will be performed with SPSS and R.

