### Trial design {8}

The trial is designed as a multicenter superiority parallel group trial with a 1:1 allocation ratio. Randomization will take place on an individual basis.

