### Outcomes {12}

The primary outcome of the study is the congruence between the preferred and actual role in the decision-making process as measured by the Control Preferences Scale (CPS) [40, 41]. Secondary outcomes are satisfaction with the actual role, decisional conflict (Decisional Conflict Scale (DCS)) [42, 43], knowledge and attitude towards preventions strategies (Multidimensional Measure of Informed Choice (MMIC)) [44, 45], stage of decision-making (Stage of Decision Making Scale (SDMS)) [46, 47], symptoms of anxiety and depression (Hospital Anxiety and Depression Scale (HADS)) [48, 49], coping self-efficacy (Coping Self-Efficacy Scale (CSES)) [50], subjective impact of the test result (Impact of Event Scale (IES)) [51, 52], and self-concept of *BRCA1/2* carriers (BRCA Self-Concept scale (BRCA-SC)) [53]. The instruments that will be used to measure these outcomes will be obtained at three different time points. Baseline measures will be obtained before randomization within a week of inclusion in the study, t1 measures will be obtained 12 weeks after inclusion, and t2 at 6 months after inclusion in the study. Table 1 displays the outcome parameters and time points for outcome measurements.

**Table 1 Tab1:** Outcome parameters

	Study period						
	Enrolment		Allocation	Post-allocation			
Timepoint		Directly after inclusion		1 week after inclusion	Within 3 weeks after inclusion	12 weeks after inclusion	6 months after inclusion
Enrolment							
Eligibility screen	X						
Informed consent	X						
Allocation			X				
Interventions							
Decision aid				X			
Decision coaching					X		
Assessments		t0				t1	t2
Control Preferences Scale							
Desired role		X					
Actual role						X	
Satisfaction						X	
Decisional Conflict Scale		X				X	X
Multidimensional Measure of Informed Choice							
Attitudes		X				X	X
Knowledge		X				X	X
Stage of Decision Making Scale		X				X	X
Hospital Anxiety and Depression Scale		X				X	X
Coping Self-Efficacy Scale		X				X	X
Impact of Event Scale		X				X	X
BRCA Self-Concept Scale		X				X	X

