#### Congruency between desired and actual role in the decision process and satisfaction with the actual role

The congruence between the desired and actual role in the decision-making process and satisfaction with the actual role played is assessed by the Control Preferences Scale (CPS) [40, 41]. The CPS was designed to measure the degree of control that patients want to assume in physician–patient interactions and has often been used in studies on decision support. The items were adapted to the decision situation of *BRCA1/2* mutation carriers by replacing the term “treatment” with “prevention strategy”. The desired role will be measured at baseline and the actual role at T2 (12 weeks after inclusion). The difference between these two measurements reflects the congruence between desired and actual role. One item will be added to the CPS to measure satisfaction with the actual role played at T2.

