### Sample size {14}

The sample size calculation for the summative evaluation is based on an assumed small to moderate effect of the intervention (Cohen’s *d* = 0.3) in a two-sided *t*-test between two groups [28]. It accounts for a drop-out rate of 30%, a power of 0.8 and an alpha error of 0.05. Based on these numbers, the software G*Power [55, 56] yielded a total *n* = 398 (199 participants per group).

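### The primary t-test leaves out the pre-randomisation desired role, itself one component of the congruence score, and so forgoes a nearly free gain in precision whose size depends on how the score is defined

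*Protocol article*

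**What the plan says.** Under Statistical methods {20a}, the primary scores "will be compared using an independent samples one-sided *t*-test with the group allocation as the independent variable". No covariate is named for that test. A later sentence in the same paragraph, after the secondary outcomes, adds demographic variables as independent variables without saying for which outcome. The desired role is not mentioned there.

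The section on congruency between desired and actual role takes the desired role at baseline and the actual role at 12 weeks, and states: "The difference between these two measurements reflects the congruence between desired and actual role". It does not say whether the difference is signed, absolute or reduced to match/no match.

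Outcomes {12} fixes the timing: "Baseline measures will be obtained before randomization within a week of inclusion in the study". Baseline data and allocation, and Implementation {16c}, confirm that the group is released only after the baseline questionnaire has come back.

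Sample size {14} plans for d = 0.3 "in a two-sided *t*-test between two groups". It continues: "It accounts for a drop-out rate of 30%, a power of 0.8 and an alpha error of 0.05", and the calculation "yielded a total *n* = 398 (199 participants per group").

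**The concern.** A two-sample t-test on a difference score fixes the weight of the baseline component at one. If the score is signed, the desired role enters the outcome with its full variance, and any chance difference between the arms in desired role passes in full into the estimated effect. The plan checks baseline comparability but provides no adjustment in the primary test.

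Every randomised woman has returned the baseline questionnaire, so the covariate is available for all of them apart from item non-response. A woman without a desired role has no congruence score either, so adjusting for it excludes nobody further. Conditioning on a value fixed before randomisation does not bias the comparison. With 30% drop-out assumed and no imputation planned, only about 139 women per arm would contribute, and precision that costs nothing is worth having.

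**Working it through.** **Inputs from the article.** d = 0.3, alpha 0.05, power 0.80, drop-out 30%, 199 per group (Sample size {14}); 1:1 allocation (Trial design {8}); one-sided t-test on group alone (Statistical methods {20a}); no imputation (Protocol non-adherence and missing data {20c}).

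**Inputs not in the article, so assumed.** The correlation rho between desired and actual role, the ratio k = SD(actual)/SD(desired), and the role distributions. Five CPS response options are also assumed, because the article does not state the number.

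**1. Reproducing 398.** By the noncentral t, a one-sided 5% test with d = 0.3 and 80% power needs 139 per arm. 139/0.7 = 198.6, rounded up to 199 per group, 398 in total. This matches. A two-sided 5% test needs 176 per arm: 352/0.7 = 502.9, so 503, which does not match. The stated size therefore fits the one-sided test of the analysis section.

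**2. Power of the planned test.** Evaluable per arm: 0.7 × 199 = 139.3, taken as 139. Noncentrality = 0.3 × √(139/2) = 2.50. One-sided power is 0.802.

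**3. Variance explained, signed difference.** With A actual and P desired, Var(A − P) = s²(k² + 1 − 2k·rho), where s is the SD of P. The share explained by P is

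R² = (k·rho − 1)² / (k² + 1 − 2k·rho),

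which for k = 1 reduces to (1 − rho)/2. Adjusted noncentrality = 2.50/√(1 − R²).

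| k | rho | R² | One-sided power | Gain (points) |
|---|---|---|---|---|
| – | none (unadjusted) | 0 | 0.802 | – |
| 1 | 0.3 | 0.35 | 0.926 | 12.4 |
| 1 | 0.5 | 0.25 | 0.892 | 8.9 |
| 1 | 0.7 | 0.15 | 0.856 | 5.3 |
| 1 | 0.8 | 0.10 | 0.838 | 3.5 |
| 1 | 0.9 | 0.05 | 0.820 | 1.8 |
| 1.25 | 0.5 | 0.107 | about 0.84 | about 4 |

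For the last row: (0.625 − 1)² / (1.5625 + 1 − 1.25) = 0.1406/1.3125 = 0.107. The gain vanishes as k·rho approaches 1 (k = 1.5, rho = 0.7: R² = 0.002). It grows if the actual role varies less than the desired role (k = 0.75, rho = 0.5: R² = 0.481). Using four degrees of freedom instead of one leaves the power figures in the rho = 0.3, 0.5 and 0.7 rows unchanged to three decimals.

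**4. Absolute difference and exact match.** No closed form applies, so five-category roles were simulated with the desired role as a factor.

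- Three assumed distributions, the same cut-points for both roles, rho 0.3 to 0.7, with or without a latent half-SD shift in actual role: R² was 0.02 to 0.17 for the absolute difference and 0.015 to 0.083 for an exact match. A linear term explained only 0.00 to 0.07 of the absolute difference, because a linear term misses a U-shaped relation.
- Forty-eight settings (four assumed distributions for each role; rho 0.3, 0.5, 0.7): the one-sided gain for the absolute difference was 0 to 8.7 points and below 5 in 37 of 48. For an exact match it was at most 4.8.
- A wider grid with rho from 0 to 0.7 reached R² of 0.36 (absolute) and 0.16 (match), so these upper limits belong to the assumed settings and are not hard ceilings.

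**The case against.** The strongest reply is that nothing here is an error. An unadjusted t-test in an individually randomised 1:1 trial is valid, the sample size was computed for a t-test, and 398 reproduces exactly for the one-sided version. All of that stands. A reader might infer that the trial loses some 9 to 12 points of power. The documents do not support this. The planned 80% is delivered, and those two figures are a single assumed case (R² = 0.25) read first one-sided (8.9) and then two-sided (11.8). Two-sided power at 139 per arm is 0.703, but that shortfall comes from the separate conflict between the two-sided test in Sample size {14} and the one-sided test in Statistical methods {20a}. Missing covariates do not cause it.

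A second reply also stands. With a signed score, regressing the difference on group and desired role gives the same group coefficient as regressing actual role on group and desired role. That measures a shift in role, in which over- and under-involvement cancel, whereas the hypothesis under Objectives {7} concerns congruence. The unadjusted signed t-test has the same defect, so adjustment neither creates nor cures it. It does mean that the largest gains belong to the version of the score that fits the hypothesis least.

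A third reply is that covariates are usually left to a statistical analysis plan, and that the demographic sentence shows further modelling is intended. This carries less weight. The article does not leave the primary test open, and the desired role is not a demographic variable.

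**Conclusion.** The point holds as a recommended improvement. The primary comparison ignores a pre-randomisation variable that is one component of its own outcome, and so forgoes precision and protection against chance imbalance at almost no cost. It does not hold as a claim that the test is invalid or that the trial falls short of its planned one-sided power.

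The size cannot be derived from the documents. For a signed difference with equal variances and rho between 0.3 and 0.7, the forgone gain is about 5 to 12 points of one-sided power. It is about 2 to 4 points at higher rho or a moderately larger actual-role SD, and can approach zero. For a score that measures congruence directly, the gain is smaller: about 0 to 9 points and often below 5 for an absolute difference, and below 5 for an exact match, under the 48 simulated settings. Protection against imbalance matters most for the signed score.

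**What to change.** First, state in the section on congruency between desired and actual role how the difference is scored: signed, absolute or match/no match. The choice should serve the hypothesis of higher congruence.

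Then, in Statistical methods {20a}, make the primary analysis a linear model of that score on group, with the baseline CPS desired role as a factor (five levels, if the scale is used with five options). A factor is preferable to a linear term because it also works for an absolute score. Report the adjusted group difference with its confidence interval as the primary result, and keep the unadjusted t-test as a supporting analysis.

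The model itself takes one sentence. It needs no new data and no more women, and uses up to four degrees of freedom out of about 278 evaluable women. The sample size can stay as it is, with any gain treated as a margin.

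### The planned two-sample tests for the secondary scales name no baseline score as covariate, so precision available from the t0 measurements is given up

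*Protocol article*

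**What the plan says.** Under Statistical methods {20a} the protocol article fixes the method for the secondary outcomes: "All secondary outcomes will be analyzed via independent samples" t-tests, "Chi-square tests, or nonparametric tests in case of non-normality". It adds that "Beyond group allocation, demographic data will be used as the independent variable". The one stated use of baseline data in that section, apart from the preferred role that forms part of the primary outcome, is "Baseline data will be analyzed to guarantee comparability of both groups".

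Under Outcomes {12}, "Baseline measures will be obtained before randomization within a week of inclusion in the study". Table 1 marks the following at t0, t1 and t2: the Decisional Conflict Scale (DCS), the attitudes and knowledge parts of the MMIC, the Stage of Decision Making Scale (SDMS), HADS, CSES, IES and BRCA-SC. Satisfaction with the role played is marked at t1 only.

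The article does not say whether the t-tests use follow-up scores or change scores, and it gives no baseline to follow-up correlation for any scale.

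**The concern.** Each of the seven continuous measures (DCS, attitudes, knowledge, HADS, CSES, IES, BRCA-SC) has a value from before randomisation. Such a value usually predicts the follow-up score well, yet it has no stated role in the effect estimate. A comparison of follow-up means leaves the variance it explains in the standard error, and any chance difference between the groups at t0 is carried into the estimate in proportion to r.

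Reduced decisional conflict and psychological burden and better knowledge are listed as objectives, so precision on these scales matters. It matters more because the sample size section already allows for 30% drop-out.

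Two smaller points come from the same section. The move to a nonparametric test depends on the data and has no stated criterion, so the same scale could be summarised differently at t1 and t2. And no analysis of baseline data can guarantee comparability: randomisation provides it in expectation, and a baseline table describes what happened.

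**Working it through.** **Inputs from the protocol article.** Sample size {14} gives d = 0.3, 199 per group and a two-sided test. It also states: "It accounts for a drop-out rate of 30%, a power of 0.8 and an alpha error of 0.05". Statistical methods {20a} makes the primary comparison one-sided.

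**Inputs that are assumptions.** Correlation r between baseline and follow-up: 0.5, range 0.3 to 0.7. The effect d = 0.3 and the 30% drop-out belong to the primary outcome and are borrowed here. The sidedness of the secondary tests is not stated; two-sided 0.05 is used.

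**1. Completers per group, and the plan's own figure.** 199 × 0.70 = 139.3, so about 139. The noncentral t calculation for d = 0.3, alpha 0.05 and power 0.80 gives:
- one-sided: 139 per group; 139 / 0.70 = 198.6, so 199 per group and 398 in total, as stated;
- two-sided: 176 per group; 176 / 0.70 = 251.4, so 252 per group and 504 in total.

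The stated 398 therefore fits the one-sided test and not the two-sided one that the sample size section names. That is a separate matter. Here it only confirms 139 as the number of completers that the plan's size implies.

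**2. Variance after baseline adjustment.** With equal SDs at baseline and follow-up, the residual variance factors relative to a follow-up comparison are:
- adjustment for baseline (ANCOVA): 1 − r²;
- change score: 2(1 − r).

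The difference is 2(1 − r) − (1 − r²) = (1 − r)², which is never negative. Adjustment is therefore never less precise than the change score.

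**3. Power** at 139 per group, two-sided 0.05, with effective d = 0.3 / √(factor):

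| r | Variance cut r² | Effective d, adjusted | Power, adjusted | Change-score factor | Power, change score |
|---|---|---|---|---|---|
| no baseline used | 0 | 0.300 | 0.703 | – | – |
| 0.3 | 9% | 0.314 | 0.743 | 1.4 | 0.558 |
| 0.5 | 25% | 0.346 | 0.821 | 1.0 | 0.703 |
| 0.7 | 49% | 0.420 | 0.937 | 0.6 | 0.896 |

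**4. In numbers of women.** The unadjusted test would need 1 / (1 − r²) times as many completers for the same precision: 1.10 at r = 0.3, 1.33 at r = 0.5 and 1.96 at r = 0.7.

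**Where the arithmetic stops.** It does not apply to role satisfaction, which has no t0 value. It does not carry over directly to the four-category SDMS or to the binary rating of informed choice.

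**The case against.** The strongest reply is that nothing here is invalid. Under randomisation an unadjusted two-sample comparison is unbiased, and its standard error already allows for chance imbalance. The secondary outcomes have no power target, and the primary outcome is untouched, because preferred role is measured only at t0 and actual role only at t1. All of this stands. The point is one of efficiency.

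Several stronger readings are tempting and are not supported:

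- *That a quarter of the variance is being lost.* A reader might infer this from the usual r = 0.5, but the documents give no correlation. Only the range with its assumption can be stated.
- *That the analyses are wholly unadjusted.* The sentence on demographic data signals some modelling beyond a two-group test. The omission is certain only for the baseline score.
- *That t0 values are discarded.* Change scores are not excluded. They would use t0, but at r = 0.5 they gain nothing over follow-up scores and at r = 0.3 they lose power.
- *That the plan tests baseline differences, or puts that check in place of adjustment.* The text says only that baseline data are analysed, which a descriptive table would satisfy. Only the claim to guarantee comparability is wrong.
- *That a nonparametric test leaves no effect estimate.* Rank tests have companion estimates such as Hodges-Lehmann, and reporting mean differences is not ruled out. Chi-square and rank methods also suit the categorical items.

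It can also be said that an analysis plan not shown may add adjustment. That is possible, but the article names a method rather than deferring it, so such a plan would have to depart from the published text. Visit structure and a centre term are details that may fairly be left to that plan, and their absence is no part of this point.

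**Conclusion.** The point holds as a loss of precision on seven continuous secondary scales, not as bias and not as a threat to the primary result. For an assumed r of 0.3 to 0.7, adjusting for the t0 score cuts residual variance by 9% to 49%, and by 25% if r = 0.5. In the illustration, two-sided power rises from 0.70 to between 0.74 and 0.94 (0.82 at r = 0.5). The power figures rest on three assumptions: d = 0.3 and 139 completers per group carried over from the primary outcome, a two-sided test, and the stated range of r. With a one-sided test the unadjusted starting point would be about 0.80, but the variance reduction would be the same. Change scores, if they were meant, do worse than adjustment at every r in the range.

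No harm from the normality-triggered switch has been quantified. With about 139 per group a comparison of means tolerates moderate skew, so the switch is largely unnecessary.

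**What to change.** Amend Statistical methods {20a} before the data are analysed:

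1. For DCS, MMIC attitudes and knowledge, HADS, CSES, IES and BRCA-SC, make a baseline-adjusted comparison the main analysis. This can be ANCOVA at each visit, or one linear mixed model for t1 and t2 with arm, visit, arm-by-visit and baseline score. Report the adjusted mean difference with 95% CI at each visit.
2. Replace the switch to nonparametric tests for these scales with robust or bootstrap standard errors if residuals are skewed.
3. Keep methods suited to categorical data for the four-category SDMS, for example ordinal regression with baseline stage. Use an unadjusted or ordinal comparison for role satisfaction, which has no t0 value.
4. State that baseline data will be described by group, without the claim that this guarantees comparability.

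The cost is a change of wording. No new data are needed, and SPSS and R, which the plan already names, can fit these models.

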### Interim analyses and stopping guidelines {21b}

Interim analyses are not planned. No problems detrimental to the participants are anticipated; therefore, this trial has no formal stopping guidelines.

### Methods for any additional analyses {20b}

#### Formative evaluation

A comprehensive process evaluation from the beginning to the end of the study is necessary to understand the underlying mechanisms of the intervention, the contextual factors influencing outcome development, to ensure the generalizability of the study results, and to improve future implementations.

Although this study is no cluster-randomized trial, the formative evaluation follows Grant’s framework for designing process evaluations [57]. The framework was adapted to our study. Especially the following elements will be considered: recruitment (difference between participating and non-participating clinics; recruitment of women), implementation of the intervention (delivery to clinics and women: fidelity, dose, adaptations made, reach), and responses of the healthcare professionals (physicians and nurses) as well as included women. Furthermore, we will integrate the contextual perspective. Therefore, we will explore the context in which the trial is being conducted and examine how the intervention is introduced. This adoption of a systems lens may enable us to look at concepts like feasibility or acceptability in dynamic terms and investigate how clinic responses to interventions change over time, rather than viewing context as background noise [58]. The outcome will be interpreted in the light of these identified processes.

A mixed-methods approach will be used to collect data alongside the RCT. Quantitative data will be analyzed using descriptive statistics, qualitative data from semi-structured interviews will be tape-recorded and transcribed verbatim. Further, we will generate qualitative field notes that capture observations made during study events (e.g., training sessions, project meetings). Transcribed data, data form field notes, as well as data from open-ended questions in the questionnaires and monthly reports of the trained nurses will be imported into MAXQDA software (VERBI GmbH, Berlin, Germany) and analyzed using principles of content analysis [59].

A summary of the central questions in the process evaluation and data collection methods are presented in Additional file 1.

